The procedure and materials of each of the experimental blocks is described in next sections and in Figs. 1 and 2. In brief, in the experimental block each experimental tone (‘ascending’, ‘descending’, ‘constant’), will be presented ten times. The order in which the tones are presented will be counterbalanced across participants following a within-subject design. After the experimental block is completed, participants will be asked to repeat the task of pulling their right finger (Experiment 1) or waist sides (Experiment 2) while listening to a tone for three more trials, one trial for each feedback condition, with the presentation order randomized across participants. Participants will be asked to complete a body feelings questionnaire after each feedback condition (questionnaire block) [see Additional file 2 and 3 for more details]. Additionally, for Experiment 2, a baseline and post-experiment body size discrepancy measure will be collected. The full experimental procedure will take approximately 120 min with a 5-min rest interval between both experiments. After completing the study, a debriefing session will be carried out.

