The experimenter will use the measurements on the back of the ruler to record the fingertip and knuckle positions, rounding to the nearest 0.5 cm. After each trial, the clips are relocated. After completing the practice task, the experimental block will begin. Participants will repeat the task for thirty trials. Each experimental tone will be presented ten times. The order of trials will be randomized across participants. Participants will be given the opportunity to rest after each 10 trials.

After the experimental block, participants will be asked to repeat the task for three more trials (one for each sound condition, their order randomized across participants), in order to collect self-report measures (questionnaire block). After each trial, participants will complete a questionnaire that assesses their subjective experience during the task [see Additional file 2].

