After the experimental block, participants will be asked to repeat the task for three more trials (one for each sound condition, their order randomized across participants) in order to collect self-report measures (questionnaire block). After each trial, participants will complete a questionnaire that assesses their subjective experience during the task [see the Additional file 3]. In addition, to assess the degree of post-experiment body size discrepancy, participants will complete the Body Visualizer task. They will repeat the task for three trials, one trial for each feedback condition. The order of the trials will be randomized among participants.

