### Statistical analyses

#### Primary aim: auditory-driven changes in body perception Baseline measures

To determine differences between the groups, analyses will be performed with a Student's t-test paired comparison (for normal distribution) or Wilcoxon tests (for non-normal distribution) for ED symptomatology (EDE-Q), interoceptive body awareness (MAIA), sensory-processing sensitivity (HSPS) and body size discrepancy (Body visualizer tool).

#### Experiment 1 and Experiment 2

For the estimations of body part position/size, confidence task and items from the body feelings questionnaires we will follow a 2 × 3 ANOVA within-between interaction repeated-measures design (see Table 2). Specifically, we will use non-parametric ANOVAs on aligned rank (ART) data, suitable for ordinal data, using the R package ARTool [56]. The ANOVAs will involve a group factor with 2 levels (subthreshold EDs and controls) and a feedback condition factor with 3 levels (‘ascendent’, ‘constant’, ‘descendent’). Prior the analysis, assumptions of independence, normality and sphericity will be checked. As in [24], we will include the degree of body size discrepancy as covariate in case of significant baseline differences. Appropriate post-hoc tests will be conducted in case of significant differences.

**Table 2 Tab2:** ANOVA 2 × 3 design

Group	Feedback condition		
	Ascendent	Constant	Descendent
Subthreshold EDs	Subthreshold EDs–Ascendent	Subthreshold EDs–Constant	Subthreshold EDs–Descendent
Controls	Controls–Ascendent	Controls–Constant	Controls–Descendent

For body size discrepancy, we will follow a 2 × 3 ANOVA within-between interaction repeated-measures design (see Table 3). The ANOVAs will involve a group factor with 2 levels (subthreshold EDs and controls), a time factor with two levels (baseline and post-experiment) and a feedback condition factor with 3 levels (‘ascendent’, ‘constant’, ‘descendent’).

**Table 3 Tab3:** ANOVA 2 × 2 × 3 design

Group	Baseline	Experiment		
		Feedback condition		
		Ascendent	Constant	Descendent
Subthreshold EDs	Subthreshold EDs Baseline	Subthreshold EDs Post-experiment Ascendent	Subthreshold EDs Post-experiment Constant	Subthreshold EDs Post-experiment Descendent
Controls	Controls Baseline	Controls Post-experiment Ascendent	Controls Post-experiment Constant	Controls Post-experiment Descendent

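### The questionnaire and post-experiment avatar outcomes are taken once per tone in randomised order, but the ANOVAs omit trial position; any drift costs precision, not validity

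*Protocol article*

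**What the plan says.** **Collection.** The General experimental procedure says that, after the experimental block, participants repeat the pulling task "for three more trials, one trial for each feedback condition, with the presentation order randomized across participants", with a questionnaire after each. The Experiment 1 procedure repeats this: "three more trials (one for each sound condition, their order randomized across participants), in order to collect self-report measures (questionnaire block". The Experiment 2 procedure describes the same block for the waist and adds the post-experiment Body Visualizer: "They will repeat the task for three trials, one trial for each feedback condition. The order of the trials will be randomized among participants". The Data management section counts six questionnaires per participant (two experiments by three tones) and three post-experiment avatar scores, one per tone. Neither outcome is replicated over separate trials of the same tone.

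**Analysis.** Under Statistical analyses, Experiment 1 and Experiment 2, the questionnaire items share a 2 × 3 model with the position/size estimates and confidence ratings: "The ANOVAs will involve a group factor with 2 levels (subthreshold EDs and controls) and a feedback condition factor with 3 levels". The method is aligned-rank ANOVA. The avatar model has group, a two-level time factor (baseline, post-experiment) and tone. The only covariate is baseline body size discrepancy, entered if the groups differ on it. No model has a term for trial position, order or sequence.

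**The concern.** For these two outcomes the design is a three-period crossover with one observation per period. Participants fill in the same form, or adjust the same avatar, three times running. A change from first to third trial (first exposure to the form, anchoring on the previous answer, fatigue in a session of about 120 minutes) would be mixed into the tone contrasts of each individual. The avatar model's time factor does not help, because it separates baseline from post-experiment and not the three post-experiment trials from one another.

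Across participants, random order averages such a change out of the tone effect. Within the model as stated it remains in the residual. The tests affected are the tone effect and the group-by-tone interaction on the explicit measures, which are part of the evidence for H2 and H3. The study already concedes that its power may be low.

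**Working it through.** **The plan's own figures.** There is no power figure to reproduce: Sample size considerations says no calculation was done. It cites a benchmark (effect 0.4, power 0.80, alpha 0.05) and says the study may not meet it. That is right. For two independent groups, n = 2 × (1.960 + 0.842)² / 0.4² = 98.1, so 99 per group. With 50 per group, power is Φ(0.4 × √25 − 1.960) = Φ(0.04) = 51.6%.

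**Inputs.** From the protocol: 50 per group, three tones, one response per tone, random order. Assumed: a linear drift of d within-person residual SDs per trial, common to both groups, with d from 0 to 1.0; and a group-by-tone effect sized for 80% power when d = 0.

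**Error variance.** Two tones occupy two different positions drawn from 1, 2, 3. Of the six orders, four put them one step apart and two put them two steps apart. The variance of the position difference is therefore (4 × 1 + 2 × 4)/6 = 2. A contrast between two tones has variance 2 without drift and 2 + 2d² with drift, a ratio of 1 + d². This is 1.04 at d = 0.2, 1.25 at d = 0.5 and 2.0 at d = 1.0.

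**Power.** The group-by-tone F test has 2 and 196 df. Interaction effects of ±0.221 SD on the outer two tones give a noncentrality of 200 × 0.221² ≈ 9.8 and 80% power. Drift divides the noncentrality by 1 + d². A position term takes the drift out of the error and leaves 194 error df; power then stays at 80.0%.

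| d | Power without position, analytic | Loss against 80% |
|---|---|---|
| 0.1 | 79.6% | 0.4 points |
| 0.2 | 78.3% | 1.7 points |
| 0.3 | 76.3% | 3.7 points |
| 0.5 | 70.0% | 10.0 points |
| 0.75 | 59.7% | 20.3 points |
| 1.0 | 48.8% | 31.2 points |

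A simulation with 3,000 runs per setting agrees and fills in d = 0.35: 74.1% without the term and 78.9% with it, a gap of 4.8 points. With no drift, the term made a difference of 0.6 points (78.8% against 78.2%).

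**The planned method.** A second simulation (2,000 runs) applied aligned ranks to 7-point responses. Power without and with the term was 71.7% and 71.1% at d = 0, 71.4% and 72.4% at d = 0.2, and 64.0% and 72.0% at d = 0.5. Simulation error is about √(0.72 × 0.28/2000) = 1.0 point, so only the gap at d = 0.5 is clear.

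**Type I error.** Without the term, ordinary ANOVA rejected a true null in 4.6% to 6.0% of runs over d = 0 to 1.0, with no trend in d. Aligned ranks gave 5.3% to 6.7%, about the same with drift as without.

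**Chance imbalance.** If each order is drawn independently, the mean position difference between two tones has SD √(2/50) = 0.20 in each group. The difference between groups has SD √2 × 0.20 = 0.28 trial steps.

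**The case against.** **Randomising the order is itself accepted protection, and a condensed article need not list nuisance terms.** The first half stands, and it is why this is a precision point only. The second half does not dispose of it: the article names every factor and covariate and draws the layouts in its Tables 2 and 3, so this is a stated model that omits a factor the design randomises.

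**Drift may be small.** This stands as a limit on size. Each questionnaire block follows 20 anchor, 3 practice and 30 experimental trials, and the avatar has been adjusted at baseline. But those earlier trials collect position and confidence judgements, not the questionnaire. In Experiment 1 the first questionnaire trial is the first sight of that form.

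**The simulated model is not the avatar model.** This also stands. The avatar layout has a baseline cell without a tone, which a three-response group-by-tone model does not represent. The figures apply to comparisons among the three post-experiment trials and are only a guide to the full avatar analysis.

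**Stronger readings a reader might infer.**
- That the tone or group-by-tone results would be biased or produce false positives: randomised order rules this out on average, and the simulated rejection rates show no inflation from drift.
- That the tests of H2 and H3 as a whole are compromised: illusion strength is also measured by position and size estimates with ten averaged repetitions per tone, which this point does not touch.
- That the orders are known to be unbalanced: the protocol says only that they are randomised, so the 0.28 figure is conditional on independent draws. The sentence "The order in which the tones are presented will be counterbalanced across participants following a within-subject design" concerns the 30-trial experimental block and settles nothing for these blocks.
- That the aligned-rank ANOVA must be abandoned: the plan chose it because it suits ordinal items, and replacing it across 14 finger and 13 waist items is a larger change than this point justifies.

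**Conclusion.** The point holds as a modest, inexpensive gain in precision for two outcomes: the body feelings questionnaire in both experiments and the post-experiment avatar score. Their models leave out trial position, so any drift over the three trials stays in the error and inflates it by about 1 + d². From an assumed 80%, power falls by under 2 points for d up to 0.2, about 5 points at 0.35 and about 10 points at 0.5.

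These figures rest on a linear drift common to both groups, whose size the protocol does not give, and on a starting power that the protocol does not claim. In a study that calls all its hypotheses exploratory and discloses limited power, this is a worthwhile improvement and not a flaw that threatens the conclusions.

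**What to change.** - **Order.** For the three-trial blocks, replace unspecified randomisation with equal allocation of the six tone orders within each group (8 participants per order makes 48, plus 2 more orders for 50), and record each participant's order. Balance removes most of the chance imbalance from the estimates; the position term is still needed to take drift out of the residual.
- **Avatar score.** Use a linear mixed model with the planned factors, trial position (1, 2, 3) as a fixed effect and participant as a random effect. Baseline has no position in this sequence, so the term should apply to the post-experiment trials only.
- **Questionnaire items.** Keep the aligned-rank ANOVA if preferred, and pre-specify a companion mixed model (ordinal or linear) with group, tone, group by tone, and position. A mixed model is the natural place for the term because tone and position are not fully crossed within a person, whereas aligned ranks are built for crossed factors.

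**Cost.** A prepared order list, two error degrees of freedom (196 to 194 in the 2 × 3 layout) and some extra analysis; no added participants, visits or measurements. With no drift, the term changed simulated power by under 1 point in the linear and aligned-rank models. The ordinal mixed model was not simulated, so that figure should not be carried over to it.

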Body visualizer task [44]	To assess the ability to accurately estimate body size (body size discrepancy) as well as the effects of sound feedback on perceived body size. Participants will adjust the weight related dimension of the body of a 3D avatar displayed on the screen to correspond to their perceived body size. Accuracy will be calculated according to the formula (estimated/actual body size) × 100 also-called body perception index (BPI) [45]. Specifically, a negative value represents an underestimation, whereas a positive value represents an overestimation	X		X

Body weight will be measured to the nearest 0.1 kg/% by means of a calibrated digital body fat scale (Sinocare CW 286). The Body feelings questionnaire will be directly built into Google Form and completed on a 10.1″ Android tablet (Lenovo M10)

^†^Spanish Version of the Eating Disorder Examination Questionnaire [46]

^‡^Spanish version of the Highly Sensitive Person Scale [47]

^§^The Multidimensional Assessment of Interoceptive Awareness [48]

Inclusion criteria will be: (a) normal (or corrected) auditory acuity; (b) sex: females (sex assigned at birth); (c) females within the healthy range of BMI (between 18.5 and 24.9) in order to reduce the likelihood of medical comorbidities that could affect the results (according to the World Health Organization index (WHO) [49]). Nevertheless, we recognize that weight/body mass index is not the sole predictor of potential co-occurring medical conditions. By doing so, we also avoid a potential confounding variable reported by [24]. This is in line with the criteria of healthy participants usually used in the field of eating disorders and body illusions research (e.g., [16]). Exclusion criteria: (a) lifetime history or presence of any significant brain injury, neurological condition, auditory pathology; (b) lifetime history or presence of a mental illness measured by self-report measures and screening questions; (c) lifetime history of underweight or overweight; (d) current use of psychotropic drugs (e.g. antidepressants) or intake of recreational synthetic or natural drugs; (e) inability to understand Spanish; (f) inability to provide consent; (g) out of age range; (h) pregnant status.

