## Data analysis plan

IBM SPSS Statistics version 28.0 will be used for data inspection, descriptive and inferential statistics. All the analysis will be done by one of the investigators and it will be cross-checked by a second investigator. For transparency purposes, processed data derived from this study will be available in our OSF project.

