#### Body visualizer task

The degree of body size discrepancy will be hand-coded by the experimenter into a data sheet. Per participant, a total of four summary estimations will be calculated [(baseline body size discrepancy) + (post-experiment body size discrepancy × 3 feedback conditions: ‘ascendent’, ‘constant’, ‘descendent’)] according to the BPI index (see Table 1 for more details).

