The degree of body size discrepancy as covariate will be included in case of significant baseline differences. Similarly, assumptions of independence, normality and sphericity will be checked and post-hoc tests will be conducted if appropriate.

Following a similar approach as in [24], the proposed analysis will be based on the division of the controls vs. sub threshold group based on scores falling above or below the cut off of 2.8 on the EDE-Q. A complementary, secondary correlational analysis will be performed between estimation of body position/size measures and EDE-Q scores considering the entire sample.

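### The baseline covariate has no fixed scale or centring: as raw BPI with a covariate-by-tone term it would leave the tone main effect with about 6% power and distort the time effect

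*Protocol article*

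**What the plan says.** Under Statistical analyses, the paragraph on Experiments 1 and 2 sets out a 2 (group) × 3 (tone) repeated-measures ANOVA for position and size estimates, confidence and questionnaire items. It says that "we will use non-parametric ANOVAs on aligned rank (ART) data, suitable for ordinal data, using the R package ARTool", and then that "we will include the degree of body size discrepancy as covariate in case of significant baseline differences".

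A separate paragraph covers the avatar outcome, with group, time and tone as factors (Table 3). It names no aligned-rank method and repeats the rule: "The degree of body size discrepancy as covariate will be included in case of significant baseline differences". For software in general, the Data analysis plan says that "IBM SPSS Statistics version 28.0 will be used for data inspection, descriptive and inferential statistics".

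The score is defined in Table 1, in the Body visualizer task row: "Accuracy will be calculated according to the formula (estimated/actual body size) × 100". The next sentence of that row reads it differently: "a negative value represents an underestimation, whereas a positive value represents an overestimation". The Body visualizer task paragraph under Data management uses this index for the baseline and the three post-experiment values. Centring, and whether a covariate-by-tone term is fitted, are not mentioned.

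**The concern.** In a repeated-measures model with a covariate-by-tone term, each tone contrast is regressed on an intercept, group and the covariate. The tone main effect is then the intercept, that is, the tone effect for a person whose covariate is zero. Under the Table 1 formula, zero means a woman who judges her body to have no size. The standard error at that point is many times larger than at the centre of the data.

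The tone main effect shows whether sound moves the estimate at all. In the avatar model the time main effect shows whether the estimate shifts from before to after the experiment. There the baseline discrepancy is both the covariate and one level of the time factor. The intercept at zero then picks up regression to the mean extrapolated over the whole distance from the sample mean to zero.

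**Working it through.** **Inputs from the protocol article.** 50 per group, 100 in total; three tones; score = (estimated/actual) × 100. It gives no power figure for the tone test, so there is nothing to reproduce.

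**Assumed inputs.** The article gives no BPI means, SDs, tone effect or baseline–post correlation. The values used are group means 112/104 with SD 12, group means 108/102 with SD 10, ascending-minus-descending dz = 0.4, and covariate unrelated to tone response.

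**1. Standard error at covariate = 0.** Relative to a centred covariate it is multiplied by about √(1 + mean²/SD²).
- Raw, overall mean 108, SD 12: √(1 + 9²) = 9.06.
- Raw, overall mean 105, SD 10: √(1 + 10.5²) = 10.55.
- Signed (BPI − 100), mean 8, SD 12: √(1 + 0.667²) = 1.20.
- Signed, mean 5, SD 10: √(1 + 0.5²) = 1.12.

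For a single contrast the centred noncentrality is 0.4 × √100 = 4. Raw BPI reduces it to 4/9.06 = 0.44 or 4/10.55 = 0.38, which is close to no signal.

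**2. Simulated power of the two-degree-of-freedom tone test.**

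| Assumed BPI | Centred | Raw | Signed |
|---|---|---|---|
| 112/104, SD 12 | about 95% | about 6–7% | about 83–85% |
| 108/102, SD 10 | about 96% | about 6% | about 89% |

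Over a wider grid for a single contrast (mean 100 to 110, SD 5 to 30, dz 0.28 to 0.5), raw scoring gives 5% to 30%, against 80% to 99.9% centred.

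**3. What does not change.** At mean 105, SD 15, the simulated group-by-tone test had power 0.404 with raw and with centred scoring. With no covariate-by-tone term, the tone test kept power of 0.97.

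**4. Time effect in the avatar model.** This uses a simplified contrast, post minus baseline, with no true change, mean 108, SD 12 and correlation 0.8 (assumed). The slope of the change on baseline is 0.8 − 1 = −0.2. The residual SD is 12 × √(1 − 0.64) = 7.2, so the SE at the sample mean is 7.2/√100 = 0.72.
- Raw: intercept 0.2 × 108 = 21.6; SE 0.72 × 9.06 = 6.52; ratio 3.3.
- Signed: intercept 0.2 × 8 = 1.6; SE 0.72 × 1.20 = 0.86; ratio about 1.9.
- Centred: intercept 0.

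Simulated false-positive rates were about 89% (raw), 45% (signed) and 6% (centred).

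**The case against.** The strongest reply is that the article nowhere says the score enters uncentred. That is an inference from silence and a software default, and centring is often left to an analysis plan. The loss also needs a covariate-by-tone term that the text does not specify. For the finger and waist outcomes the named method is ARTool, not an SPSS linear model. Table 1 also describes a signed score, under which zero is an accurate perceiver and lies within the data. All hypotheses are labelled exploratory.

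Most of this stands, and it makes the point conditional. It does not remove it. With complete balanced data, a person-level covariate without the covariate-by-tone term cannot alter the tone or group-by-tone tests. The adjustment is therefore either inert for those tests or open to the scaling problem. The avatar paragraph names no aligned-rank method, so the general SPSS statement covers it. The signed reading is one of two conflicting definitions in the same table row, and it still leaves the time effect distorted. The article's caveat on power concerns differences between groups, not this within-person test.

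A reader might infer three stronger claims that the documents do not support:
- **That the finger and waist tests would lose their power.** It is unclear how a covariate would enter an aligned-rank ANOVA at all.
- **That H2, H3 or H4 fails.** H2 and H3 rest on group-by-tone, which centring does not touch. H4 contrasts finger and waist in the subthreshold group, which a tone effect pooled over both groups does not test.
- **That the fault appears whenever H1 is true.** The trigger is a significant baseline test. At a standardised difference of 0.4 with 50 per group, that occurs about half the time (power about 0.52).

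**Conclusion.** The point holds in conditional form. The article fixes the covariate, its trigger and a formula that puts it near 100, contradicts that formula in the next sentence, and says nothing on centring. Followed literally in a default SPSS repeated-measures model of the avatar outcome, the plan tests tone at an impossible value, with power of about 6% instead of about 95%. Under signed scoring the figure is about 83–89%. The time effect is also at risk, with false positives of about 89% raw and 45% signed against 6% centred.

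These sizes rest on assumed BPI means, SDs, tone effect and correlation. The direction follows from the algebra whenever the covariate mean is large relative to its SD. The time figures come from a simplified contrast, not the full Table 3 model. The problem is confined to main effects, and to the case where the covariate is triggered. It is a modest point, but the correction is free.

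**What to change.** 1. In Table 1, reconcile the BPI formula with its sign interpretation: either keep the ratio, with accurate = 100, and reword the sentence on sign, or define the score as the ratio minus 100.
2. In both covariate statements under Statistical analyses, say that baseline body size discrepancy is centred at the whole-sample mean before it enters any repeated-measures model. Alternatively, say that the tone and time main effects are taken from the model without the covariate, and that the adjusted model is used only for the group and group-by-tone terms.
3. For the outcomes assigned to ARTool, state how a covariate would enter, or that it does not.

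The cost is a few sentences. No extra data are needed, and the group-by-tone result does not depend on the centring.
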